## Abstract

**Background:**

Elevated body mass index (BMI) represents a risk factor for cancer-related fatigue (CRF). Weight loss interventions are feasible and safe in cancer survivors, leading to improved cardio-metabolic and quality of life (QOL) outcomes and modulating inflammatory biomarkers. Randomized data are lacking showing that a lifestyle intervention aimed at weight loss, combining improved diet, exercise, and motivational counseling, reduces CRF. Motivating to Exercise and Diet, and Educating to healthy behaviors After breast cancer (MEDEA) is a multi-center, randomized controlled trial evaluating the impact of weight loss on CRF in overweight or obese survivors of breast cancer. Herein, we described the MEDEA methodology.

**Methods:**

Patients (*N* = 220) with stage I–III breast cancer and BMI ≥ 25 kg/m^2^, within 12 months of primary treatment, and able to walk ≥ 400 m are eligible to enroll. Participants are randomized 1:1 to health education alone vs. a personalized telephone-based weight loss intervention plus health education. Both arms receive a health education program focusing on healthy living. Patients in the intervention arm are paired with an individual lifestyle coach, who delivers the intervention through 24 semi-structured telephone calls over 1 year. Intervention goals include weight loss ≥ 10% of baseline, caloric restriction of 500–1000 Kcal/day, and increased physical activity (PA) to 150 (initial phase) and 225–300 min/week (maintenance phase). The intervention is based on the social cognitive theory and is adapted from the Breast Cancer Weight Loss trial (BWEL, A011401). The primary endpoint is the difference in self-reported CRF (EORTC QLQ-C30) between arms. Secondary endpoints include the following: QOL (EORTC QLQ-C30, -BR45, -FA12), anxiety, and depression (HADS); weight and BMI, dietary habits and quality, PA, and sleep; health care costs (hospital-admissions, all-drug consumption, sick leaves) and cost-effectiveness (cost per quality-adjusted life-year); and patient motivation and satisfaction. The primary analysis of MEDEA will compare self-reported CRF at 12 months post-randomization between arms, with 80.0% power (two-sided *α* = 0.05) to detect a standardized effect size of 0.40.

**Discussion:**

MEDEA will test the impact of a weight loss intervention on CRF among overweight or obese BC survivors, potentially providing additional management strategies and contributing to establish weight loss support as a new standard of clinical care.

**Trial registration:**

ClinicalTrials.gov
NCT04304924

## Background

Over 80% of patients with early-stage breast cancer can nowadays expect long-term disease-free intervals after primary treatment. As a result, breast cancer survivors currently make up a substantial proportion of the population, as almost three million women in the United States of America (USA), two million in Europe, and 250,000 in France live with a history of breast cancer [1–3]. Improved survival rates have led to the emergence of a number of new, often unmet, clinical needs in survivorship care. Particularly, those related to the management of late and chronic side effects of cancer therapies and treatment-related symptoms represent key priorities [4].

Cancer-related fatigue (CRF) is one of the most common and persistent *sequelae* of breast cancer treatments [5], with a prevalence reaching 30–40% 1 year and up to 20% 10 years after treatment completion [6–9]. CRF is a complex and multifaceted syndrome, described as heavily distressing and impactful from a patient’s perspective. Its subjective expressions not only include generalized weakness and physical manifestations, but also emotional lability and loss of capacity to concentrate, which can interfere with normal functioning in a multitude of life domains spanning from usual daily activities, job tasks, and social relationships [8, 10–17].

### Excess body weight and CRF

The epidemic of overweight and obesity is a relevant public health issue in the general population worldwide, increasingly among breast cancer patients. Data suggest that up to 75% of women in the USA and 50% in Europe are overweight or obese at the time of breast cancer diagnosis [18–20], and additional weight gain after often results from breast cancer treatments [21–23].

Evidence has demonstrated a link between obesity and CRF, with data showing that elevated body mass index (BMI) represents a risk factor for CRF [11, 13, 24–29]. In a longitudinal study of women with early-stage breast cancer, BMI was significantly associated with CRF at the 42-month post-treatment assessment [11], and higher BMI also emerged as an independent predictor of membership to the high-level fatigue group in a study evaluating patterns of CRF after breast cancer treatment [24]. BMI significantly predicted chronic and persistent CRF for up to 2.5–7 years post-breast cancer diagnosis [25]. In addition, among white women with breast cancer enrolled in the Women’s Healthy Eating and Living (WHEL) Study, obesity was associated with significantly worse vitality (i.e., fatigue), compared to non-obese status [26, 27]. More recently, higher BMI was a risk factor for severe CRF in the prospective multicenter CANTO cohort study [6]. 

### Other risk factors and correlates of CRF

Previous literature highlighted several other correlates of CRF, including biobehavioral, psychological, and biological factors [13]. Relevant risk factors for the development and persistence of CRF among cancer survivors include pre-treatment fatigue, emotional distress (anxiety and depression), sleep problems, and physical inactivity and sedentary behavior [9, 13, 30, 31]. Concomitant medical conditions, comorbidities, inadequate nutrition, and symptoms such as uncontrolled pain and persistent sleep problems can also contribute to CRF [6, 30, 31].

Furthermore, although the etiology and biological substrate of CRF is not completely understood, a positive association between cytokine deregulation and increased CRF has been demonstrated. Survivors with persistent CRF have indeed been found to have increased expression of genes encoding pro-inflammatory markers or other mediators of immunologic activation [13, 32–36]. Chronic inflammatory alterations are common in individuals with higher adiposity. In obese individuals, the adipose tissue is expanded and reprogrammed, with specific metabolic activations leading to inflammatory changes in the local *milieau*. Additional interactions occur between local microenvironment and dysregulation in systemic biology, promoting a generalized inflammatory activity [37]. In this context, the enhanced pro-inflammatory cytokine network existing among individuals with higher BMI may be in part responsible for different alterations linked to CRF, including cellular immune system and neuroendocrine dysregulation [13].

### Weight loss interventions among breast cancer survivors

A number of studies looked at the feasibility and benefits of weight loss interventions in cancer survivors [38–44]. In-person or remotely delivered weight loss interventions are now deemed feasible and also safe in breast cancer survivors with excess body weight.

Examples of completed studies of large lifestyle interventions conducted in the USA among overweight or obese breast cancer survivors include the Lifestyle Intervention Study for Adjuvant Treatment of Early breast cancer (LISA) and the Exercise and Nutrition Enhance Recovery and Good Health for You (ENERGY) studies [45, 46]. These individualized interventions incorporating goals of caloric deficit and increased PA led to significant and greater weight loss across BMI strata and showed great potential in improving a number of outcomes for breast cancer survivors compared to delivery of general health and weight loss information alone. For example, a mean weight loss of 4–5 kg in the LISA intervention and of 6% of baseline in the interventional arm of ENERGY were linked to a more likely preservation of physical function, greater increases in physical condition, and improvement in a multitude of functional and symptom domains [45, 46].

More recently, the Alliance for Clinical Trials in Oncology Breast Cancer Weight Loss Trial, also known as A011401 (BWEL, NCT02750826, PI [name]) started in the USA and Canada. BWEL is a National Cancer Institute-funded phase III randomized trial evaluating the effect of a weight loss program on cancer recurrence among over 3000 overweight and obese women with stage II to III breast cancer across over 1000 institutions. The BWEL weight loss intervention is standardized using the approaches developed as part of the Diabetes Prevention Program (DPP) [45] and the LISA study, focusing on diet, PA, and motivational factors [47]. BWEL is primarily testing the impact of weight loss on invasive disease-free survival (IDFS) among overweight (BMI ≥ 27 kg/m^2^) patients with stage II–III hormone receptor (HR)-positive, human epidermal growth factor receptor (HER)2-negative breast cancer. A subset study within BWEL will also assess the impact of the intervention on health behaviors and PROs, including CRF [48].

These interventional weight loss studies also provide data demonstrating the feasibility of conducting a lifestyle intervention for cancer survivors in a cooperative group setting.

### Study rationale

Weight loss has been shown to have several health benefits for cancer survivors with elevated BMI, such as leading to a better quality of life and lower rates of cardio-metabolic comorbidities including heart disease and diabetes [49]. Studies also suggest that there is rationale to test intentional weight loss during the early survivorship period as a strategy to mitigate CRF, often developing as one of the many downstream *sequelae* of primary breast cancer treatment. Recently, observational evidence from the French CANcer TOxicity (CANTO) Study showed that compared to the pre-treatment period and respective to women whose weight increased or remained stable, obese women who lost weight reported either improvements or more favorable variations in PROs for several domains of quality of life, including CRF [50, 51]. Much remains to be learned about the relationship between weight loss and CRF, including about the biologic changes that could mediate the relationship between obesity, weight change, and CRF. Previous studies suggested that weight loss may determine a modulation in inflammatory mediators, including leading to changes in levels of IL-6, TNF-α, and C-reactive protein, which had been associated with increased CRF [13, 52], and therefore contribute to CRF mitigation.

Motivating to Exercise and Diet, and Educating to healthy behaviors After breast cancer (MEDEA) is a randomized controlled trial (RCT) building on the personalized weight loss intervention of the BWEL study. Specifically, MEDEA (1) focuses on overweight and obese adult patients with a BMI ≥ 25 kg/m^2^ recruited after their initial breast cancer (stages I–III, HR±/HER2±) treatment; (2) implements an adapted version of the BWEL intervention that includes modifications to the length and content of the intervention, as well as language and substantial cultural adaptation; (3) primarily aims to evaluate the impact of the personalized telephone-based weight loss intervention on post-treatment CRF (and secondarily on quality of life and several other general and breast cancer-specific outcomes); and (4) may help develop a model for trials testing the impact of lifestyle changes on outcomes of breast cancer survivors outside the USA.

The MEDEA Study builds on the hypothesis that a combined lifestyle intervention of weight loss, incorporating multiple components of PA, nutritional counseling, and motivational support improves CRF among overweight and obese survivors of breast cancer. The mechanisms through which such intervention may reduce CRF are several, including that interventional components are able to target or modulate multiple contributing factors for CRF. Among the components of the MEDEA intervention, PA is the most studied and effective strategy for reducing CRF both during and after primary breast cancer treatment, as demonstrated by a number of clinical trials and metanalyses. Evidence also suggests that PA may help reduce physical dysfunction, emotional distress, pain, and sleep problems, which are frequent correlates of CRF, and act on the modulation of inflammatory mediators of CRF. In addition, nutritional counseling, while targeting caloric restriction and setting daily caloric intake limits, aims at maintaining a high-quality diet that can help identify and correct nutritional imbalances that can be associated with elevated CRF. Finally, motivational support may activate patient empowerment, allow to focus on intervention goals, and help reduce maladaptive thoughts, which are common in patients with CRF [30, 31, 53–56].

In this manuscript, we present the MEDEA Study methodology.

## Methods

### Study objectives

#### Primary objective

The primary objective (objective 1) of the MEDEA trial is to compare the effect of a personalized telephone-based weight loss program based on motivational coaching, exercise, and diet versus a standard health educational program control on CRF of overweight or obese breast cancer patients (reported by patients using the European Organisation for Research and Treatment of Cancer (EORTC) Quality of life Questionnaire (QLQ)-C30) [57, 58].

#### Secondary objectives

Secondary objectives of MEDEA include the following: secondary objective 1—the evaluation of the impact of the weight loss intervention on (1.1) specific CRF dimensions, including physical, emotional, and cognitive CRF; (1.2) QOL, including domains such as global health status, emotional, social, role, cognitive function, insomnia, pain, body image, and systemic therapy side effects; (1.3) sleep quality; and (1.4) anxiety and depression, weight and BMI, dietary habits and quality, and PA; secondary objective 2—the dissemination/implementation of the intervention, adapted from a US setting, in the French health care setting; secondary objective 3—health care costs (hospital admissions, all-drug consumption, sick leaves), cost-effectiveness (cost per quality-adjusted life-year QALY), and patient motivation and satisfaction; and secondary objective 4—adverse musculoskeletal events including fractures, sprains, tendon, or ligament injuries, and orthopedic surgeries are assessed (safety).

#### Exploratory objectives

MEDEA also has the following exploratory objectives: exploratory objective 1—assess the impact of the weight loss intervention on cancer-related outcomes (IDFS and overall survival [OS]); exploratory objective 2—assess the adherence to intervention by qualitative and quantitative evaluation. For the qualitative assessment, focus groups will be performed with selected study participants to understand barriers and facilitators to uptake and adherence to the intervention, including satisfaction and suggestions for improvement regarding the weight loss program. Focus groups are envisioned at least once halfway through the intervention (month [M] 6) and once at the completion of the intervention (M12). Table 1 summarizes MEDEA Study outcomes.

**Table 1 Tab1:** MEDEA Study outcomes, measures, and assessment

Outcome type	Outcome		Measure	Type of assessment	Schedule of data collection			
					Baseline, M0	M6	M12	M18
**Primary**	**Cancer-related Fatigue**	**Global fatigue**	EORTC QLQ-C30^1^	Self-reported	X	X	X	X
**Secondary**	**Cancer-related Fatigue**	**Fatigue dimensions: physical, emotional, cognitive**	EORTC QLQ-FA12^2^	Self-reported	X	X	X	X
	**Quality of life, anxiety, and depression**	**Other quality of life domains***	EORTC QLQ-C30^1^	Self-reported	X	X	X	X
			EORTC QLQ-B45^3^	Self-reported	X	X	X	X
		**Anxiety/Depression**	HADS^4^	Self-reported	X	X	X	X
	**Health behaviors**	**Dietary habits**	Food questionnaire^5^	Self-reported	X	X	X	X
		**Physical activity**	WHO GPAQ-16^6^	Self-reported	X	X	X	X
		**Intensity of physical activity**	Actigraph Accelerometer^7^	Device-based	X	X	X	X
		**Energy expenditure**	Actigraph Accelerometer^7^	Device-based	X	X	X	X
		**Daily steps**	Actigraph Accelerometer^7^	Device-based	X	X	X	X
	**Weight and body composition**	**Weight**	Clinical visit	Hospital-based	X	X	X	X
		**Body mass index**	Clinical visit	Hospital-based	X	X	X	X
		**Waist and hip circumference**	Clinical visit	Hospital-based	X	X	X	X
	**Cost-effectiveness**	**Length of all-cause hospitalizations**	Direct medical costs	**	Throughout the whole study duration			
		**Drug consumption:** antidepressants, anxiolytics, pain-killers, and anti-inflammatory drugs (name, start date, duration of use)	Direct medical costs	**	Throughout the whole study duration			
		**Sick leave** (number, duration, and reason)	Indirect costs	**	Throughout the whole study duration			
		**Utility/QALY**	EuroQol 5D 3L^8^	Self-reported	X	X	X	X
**Exploratory**	**Survival outcomes**	**Invasive DFS**	Relapses	**	Throughout the whole study duration			
		**OS**	Death	**	Throughout the whole study duration			
	**Satisfaction and adherence**	Motivation and satisfaction with the intervention	Qualitative	Focus group	Halfway through the intervention (month 6) + once at intervention completion (month 12)			
		% delivered/planned phone calls % patients who achieve intervention goals % phone calls/total by patient/coaches	Quantitative	Centrally assessed (study manager)	End of study			

^6^Global Physical Activity Questionnaire Analysis Guide GPAQ Analysis Guide Global Physical Activity Questionnaire (GPAQ) Analysis Guide

^8^EQ-5D

*Including: Global health status, physical, emotional, social, role, cognitive function, Pain, Insomnia, Nausea/Vomit, Dyspnea, Appetite Loss, Constipation, Diarrhea, Financial difficulties, Body Image, Future perspective, Sexual function and enjoyment, systemic therapy side effects, arm and breast symptoms, endocrine therapy, skin, and sexual symptoms

**National health, insurance, hospital-based records, ad hoc questionnaire. *M* month

### Study design

MEDEA is a RCT evaluating the effect of health education alone vs. weight loss intervention plus health education on CRF in overweight and obese women with early-stage breast cancer. Patients are offered to participate in this study during routine consultations. Participants are randomized to a standard health education program (arm 1 control) vs. a 1-year personalized telephone-based health education weight loss follow-up (arm 2 interventional). A permuted block randomization is applied in a 1:1 randomization ratio using a block size of 4. Stratification occurs on the basis of BMI at diagnosis (overweight [BMI 25.0–29.9 kg/m^2^] vs. obese [BMI ≥ 30.0 kg/m^2^]), age (≤ 50 vs. > 50 years), and receipt of endocrine therapy (yes vs. no) (Fig. 1).

**Fig. 1 Fig1:**
[figure not shown]
MEDEA Study design. BMI, body mass index

To ensure allocation concealment, patients who have signed the informed consent and fulfilled all eligibility criteria will be randomized directly online using the Trialmaster randomization module. Patients are randomized for either arm after the accrual visit. Patients are enrolled through local clinic sites, and the weight loss intervention is delivered remotely by trained study coaches. Target enrollment is 220 patients.

### Eligibility

#### Inclusion criteria

Patients are eligible if they have histologically confirmed stage I–III breast cancer without evidence of distant metastatic or locally recurrent disease at inclusion. Participants with a history of invasive breast cancer in the 5 years prior to study registration other than the current diagnosis are ineligible for enrollment. Prior ductal carcinoma in situ (DCIS) at any time does not make a patient ineligible. Subjects must have a BMI ≥ 25 kg/m^2^, either objectively assessed at the time of eligibility evaluation or reported in the medical records within 56 days prior to study registration. All adjuvant or neoadjuvant chemotherapy, radiation, and surgery must have been completed no more than 12 months before enrollment. Patients may have breast reconstruction during protocol participation, but definitive breast cancer surgery must be completed prior to registration. Biologic therapy, hormonal therapy, and bisphosphonates are acceptable to be ongoing while on study. Participants should have an ECOG Performance Status of ≤ 1 and self-reported ability to walk at least 400 meters (at any pace). Each participant should understand, sign, and date the written informed consent form prior to any protocol-specific procedures and be able and willing to comply with the study visits and procedures as per protocol. Patients must be able to read and speak French to be eligible for inclusion.

#### Non-inclusion criteria

Participants in both arms are allowed to pursue weight loss and PA programs on their own, but participation in another weight loss, PA, or dietary intervention clinical trial at a time is not allowed. Comorbid conditions, such as other malignancy, diabetes, inflammatory bowel disease, history of severe cardiovascular, respiratory, or musculoskeletal disease that would preclude adherence to the study diet or PA program or significantly affect the physical status or the ability to give an informed consent make a patient ineligible for enrollment. Secondary overweight or obesity must not be documented or suspected at the time of enrollment. Chronic consumption of corticosteroids or self-reported pregnancy or intent to become pregnant in the year after enrollment also represents ineligibility criteria.

#### Withdrawal criteria

Premature discontinuation of study intervention does not necessarily mean the patient prematurely discontinues its participation in the study. (1) Withdrawal criteria from study intervention. A patient will not receive any further study intervention if any of the following occurs: request from the patient not to receive further intervention; withdrawal of consent, or lost to follow-up; adverse events or any condition incompatible with the continuation of the study intervention according to the judgment of the investigator; any medical event requiring administration of an unauthorized concomitant treatment; pregnancy or intent to become pregnant; subject non-compliance to study procedures that in the investigator and/or sponsor judgment warrants withdrawal; study terminated by the sponsor; patients with disease recurrence at any site, or new invasive cancer diagnosis, can continue the intervention if they wish, and if it is considered appropriate by physician discretion. Patients who are withdrawn from further receipt of study intervention will continue to have *follow-up visits.* (2) Withdrawal criteria from the trial. Reasons for withdrawal from the trial may include lost to follow-up, consent withdrawn, disease recurrence or new invasive cancer diagnosis, and death.

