Participants in both study arms are asked about the following musculoskeletal events during each follow-up visit: fractures, sprains, tendon or ligament injuries, and orthopedic surgeries. Non-solicited adverse events such as post-surgical wound infections or side effects from hormonal therapy such as hot flashes are not required to be reported for this trial.

Adherence to the intervention is measured by the number of completed phone calls/total number of calls scheduled. To define the intervention as completed, a minimum of 16 calls have to be completed. Satisfaction with the intervention will be also assessed with qualitative analyses and dedicated focus groups.

IDFS is defined as the time from randomization to any one of the following: distant, invasive, or locoregional recurrence; ipsilateral or contralateral invasive breast cancer; second primary invasive cancer (non-breast cancer other than basal or squamous cell carcinoma of the skin that has been adequately treated, and carcinoma in situ of the cervix); or death from any cause. Overall survival is defined as the time from randomization to death from any cause. Patients who withdraw consent to be followed are censored at that time point, and patients who are lost-to-follow-up are censored at the time point they were last determined to be disease-free.

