
### Statistical considerations

Previous meta-analyses indicated that exercise was more effective than control in reducing CRF, with a standardized effect size ~ 0.40 [31, 65–67], but there are limited data on the effect of lifestyle interventions aimed at weight loss on CRF among overweight or obese patients. To detect an effect size of 0.40, a sample size of 101 evaluable patients per arm will provide 80.0% power using a two-sided α = 0.05, two-sample test. The primary test statistic for inference is the time-by-treatment interaction effect in a linear mixed model. This effect size (0.40) is considered as small to moderate by Cohen [68]. Taking some potential drop-out into account, the final sample size for this study is inflated to 220 patients. The primary comparison of CRF among intervention assignments will be performed in the intent-to-treat population of all randomized patients (i.e., all analyses will retain each participant in the group he was randomly assigned regardless of missing data or drop-out status).

The primary analysis of MEDEA will compare the primary endpoint of CRF scores at the M12 post-randomization time point between arms. This comparison between arms will employ a linear mixed model with random patient effect using time as a categorical variable, treatment arm, and a treatment by time interaction with patient-reported CRF measured by appropriate EORTC QLQ-C30 subscale scores. In a sensitivity analysis, baseline characteristics will be added as fixed covariates to the model.

All other measures/time points/analyses will be considered secondary or exploratory analyses. Similar analyses as those specified for the primary endpoint will be performed for other scales. For binary endpoints, chi-squared tests will be used. Further analyses will include analyses of continuous endpoints using mixed-effects models and binary endpoints using generalized estimating equations. The analyses of objectives including IDFS as an endpoint are performed in an intention-to-treat manner.

For the primary analysis of MEDEA (primary endpoint of global CRF), two-sided *p*-values < 0.05 will be considered statistically significant. All other endpoints are considered secondary or exploratory, with no *p*-value adjustment for multiple testing. For interpreting the clinical significance of effects, 0.2, 0.5, and 0.8 standard deviation effects will be considered as small, moderate, and large, respectively [68].

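### Recurrence or new cancer may end trial participation and so M12 fatigue data, and the single lost-to-follow-up censoring date suits IDFS but not OS

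*Protocol article*

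**What the plan says.** The Withdrawal criteria section of the protocol article separates stopping the intervention from leaving the trial.

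- Under part (1), on the intervention, "patients with disease recurrence at any site, or new invasive cancer diagnosis, can continue the intervention if they wish", provided the physician considers it appropriate.
- Part (1) also keeps follow-up visits for those who stop, in the sentence that begins: "Patients who are withdrawn from further receipt of study intervention will continue to have".
- Part (2), on the trial itself, reads: "Reasons for withdrawal from the trial may include lost to follow-up, consent withdrawn, disease recurrence or new invasive cancer diagnosis, and death".

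Statistical considerations says of the intent-to-treat population that "all analyses will retain each participant in the group he was randomly assigned regardless of missing data or drop-out status".

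Study measures defines IDFS first, then OS: "Overall survival is defined as the time from randomization to death from any cause". One censoring sentence follows both definitions. It has two clauses. The first deals with withdrawn consent: "Patients who withdraw consent to be followed are censored at that time point". The second sets the date for losses to follow-up: "patients who are lost-to-follow-up are censored at the time point they were last determined to be disease-free". No separate rule is given for OS.

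Table 1 lists relapses and deaths as collected over the entire study. Its footnote gives the sources: "National health, insurance, hospital-based records, ad hoc questionnaire". IDFS and OS are exploratory.

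**The concern.** Three of the reasons in part (2) (loss, withdrawn consent, death) end data collection by their nature. Recurrence and new cancer do not. A patient may be judged fit to go on with coaching and yet be withdrawn from the trial that measures its effect. The section does not say how a site should choose.

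At stake for the primary endpoint is the M12 fatigue score. A relapse between M6 and M12 may well raise fatigue. If the patient leaves, her M12 score is missing for a reason that the primary model (arm, time, their interaction, random patient effect) does not contain. The option to continue coaching exists only in the intervention arm, so retention after relapse could differ by arm. That is an inference; the article does not say so.

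At stake for OS is follow-up time. The date last known disease-free is a sensible censoring date for an endpoint that includes recurrence. For death from any cause it is too early in any patient who relapsed, was later seen alive, and was then lost.

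**Working it through.** **1. The plan's own sample size.** Inputs from Statistical considerations: effect 0.40 SD, two-sided alpha 0.05, power 80%, 101 evaluable per arm, total 220.

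- Normal approximation: n = 2(1.960 + 0.842)² / 0.40² = 98.1, so 99 per arm. The t-test gives 99.08, so 100 per arm.
- Power at 101 per arm: 81.1% (normal) or 80.8% (t-test). The stated figure is reproduced closely.
- Implied drop-out allowance: 220 − 202 = 18 patients, 18/220 = 8.2%. The article states no rate.

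**2. Power if every such patient leaves.** The article gives no recurrence rate, so 1-5% by M12 is an assumption. These losses are put on top of the 18, which is the harsher case.

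Evaluable per arm = (220 − 18 − 220r)/2; power from the two-sample t-test at 0.40 SD.

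| Assumed rate r | Patients lost (220r) | Evaluable per arm | Power |
|---|---|---|---|
| 0 | 0 | 101 | 80.8% |
| 1% | 2.2 | 99.9 | 80.3% |
| 2% | 4.4 | 98.8 | 79.9% |
| 3% | 6.6 | 97.7 | 79.4% |
| 5% | 11.0 | 95.5 | 78.5% |

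The cost is 0.5 to 2.3 points of power.

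**3. Bias in the M12 difference.** Let d be the excess fatigue, in SD, of patients with the event over those without it (assumed 0.5-1.0). Leaving out a share p lowers the observed arm mean by p × d. The between-arm bias is (p₁ − p₂) × d.

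- Equal rates: 0.
- 3% vs 2%, d = 1: 0.01 × 1 = 0.01 SD.
- 5% vs 3%, d = 0.5: 0.02 × 0.5 = 0.01 SD.
- 5% vs 3%, d = 1: 0.02 × 1 = 0.02 SD.
- 5% vs 2%, d = 1: 0.03 × 1 = 0.03 SD.

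The largest of these is 0.03/0.40 = 7.5% of the target effect.

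**4. The censoring rule applied to OS.** Take an illustrative patient who relapses at M9, is seen alive at M15 and is then lost.

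- IDFS: the event is at M9, and the later loss is irrelevant.
- OS, rule as written: censored at the last disease-free date, which is before M9.
- OS, by its definition: she was at risk of death and known alive until M15.

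The rule removes more than 15 − 9 = 6 months of known survival, in the period after relapse. The consent-withdrawal clause does not have this fault, because it censors at the time of withdrawal.

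**The case against.** The strongest reply is that nothing here is a strict contradiction. Part (2) says the reasons may include recurrence, and part (1) says such patients can continue. Both are permissive, so one patient may stay and another leave. That stands: the fault is a rule left open, not two rules that cannot both be followed.

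A reader might infer that the intent-to-treat principle is breached. It is not. The sentence governs the arm in which a patient is analysed and expressly foresees drop-out, and the M0 and M6 scores of a patient who leaves still enter the mixed model. What remains is that it does not replace an M12 score.

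A reader might also infer that deaths after recurrence go unrecorded and that the OS comparison is void. The document does not support this. Table 1 draws relapse and death from national health, insurance and hospital records as well as a questionnaire, and no passage says that this stops at recurrence. But those records do not supply self-reported fatigue, and they do not change the censoring date.

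It can be said that the disease-free wording was meant for IDFS only, and that fuller censoring rules may sit in a document not shown. Possibly so. But the sentence follows the OS definition directly and is the only rule stated, so as written it covers both. Finally, the 8.2% allowance may already cover recurrences. In that case the power loss in the table is overstated.

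**Conclusion.** Both points hold as defects of stated rules, and both are modest.

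For fatigue, the withdrawal text permits avoidable missing M12 scores linked to an event plausibly related to the outcome. Under the assumptions of a 1-5% event rate, all such patients leaving, and 0.5-1.0 SD more fatigue, the cost is at most about 2 points of power. Bias is zero with equal rates and about 0.01-0.03 SD if rates differ by 1 to 3 percentage points. This would not by itself overturn a result near 0.40 SD. None of these rates comes from the document.

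For OS, the lost-to-follow-up date is wrong if applied as written, because it discards known survival time after relapse. The size cannot be given, since the article states neither relapse nor loss rates. The endpoint is exploratory, and how many patients are affected depends on how completely records are linked.

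The text supports saying that fatigue scores may be lost. It does not support saying that fatigue and death data are lost.

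**What to change.** 1. Reconcile the two parts of Withdrawal criteria. For data collection, state that recurrence or new invasive cancer alone does not end the scheduled M6, M12 and M18 questionnaires or vital-status follow-up, unless consent is withdrawn. Whether the intervention continues is for the investigators to reconcile.
2. Give OS its own censoring rule: date last known alive for patients lost to follow-up. Keep the date last known disease-free for IDFS only.

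The cost is a short note to sites and one sentence in the analysis plan. The questionnaires are already in the Table 1 schedule. On timing, the article reports accrual completed in 2021, so the last M12 visits fall by the end of 2022 and the last M18 visits by mid-2023. The site note helps only for visits still to come. If it is too late, report by arm how many patients left because of recurrence or new cancer. The OS rule can be corrected at analysis in either case.
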